### Outcomes

#### Primary outcome

The primary outcome in this study is the individual’s functional capacity, assessed by the distance in meters the patient can walk over 6 min, performing the 6-minute walk test. The 6mWT is a predictor of morbidity and mortality among COPD patients, it is a simple clinical exercise test for the objective evaluation of functional exercise capacity improvement in COPD, which measures the distance a patient can quickly walk on a flat hard surface in 6 min [48, 49]. .

### Secondary outcomes

The secondary outcomes are dyspnea, Health-Related Quality of Life (HRQoL), exacerbations, symptoms, anxiety and depression, and physical activity.

Dyspnea will be assessed by the modified Medical Research Council (mMRC) scale [32]. This is a widely used scale with four items in which the higher the value, the greater the dyspnea intensity.

HRQoL will be assessed by the Eq. 5D [50]; The EuroQol instrument is intended to complement other quality-of-life measures and to facilitate the collection of a common data set for reference purposes.

The number of exacerbations measured by hospital admissions and emergency department visits due to COPD exacerbation will be evaluated via consultation of electronic records [51];

Symptoms will be measured by the Clinical COPD Questionnaire (CCQ) [52, 53] and the COPD Assessment Test (CAT) [54];

Anxiety and depression will be assessed by the Hospital Anxiety and Depression Scale (HADS) [55];

A pedometer (Yamax EX 510®), validated in COPD, will assess physical activity by monitoring the average daily steps [17, 41, 56]. Participants will wear the device for seven consecutive days during waking hours (except when bathing or sleeping).

Regular physical activity (p.a.) is associated with important health benefits and may prevent the development and progression of chronic diseases.

### Other measures

We will quantify the number of times an intervention is carried out and how long it takes to achieve the intended effect.

### Sample size and statistical methods

The minimum sample size required was calculated considering the final comparison between the two groups regarding the primary outcome and the inclusion of five covariates to adjust for potential comparison biases between the groups.

We will perform an intention-to-treat analysis. Therefore, stipulating ANCOVA as the statistical procedure to be used, a significance level of 5%, a test power (1-β) of 80%, an average effect magnitude (f = 0.25, corresponding to $$\eta$$^2^= 0.06, 6% of the variability of the dependent measure under evaluation to be explained by the group) and five covariates in the model, the sample size to be collected will be 128 participants, which corresponds to 69 participants for each group.

Considering that we may have 20% follow-up losses, the sample size to be collected will be 160 participants (80 per group).

### Data analysis

The sample size covers the sample dimension necessary for applying a mixed ANCOVA. The group will be considered an inter-subject factor, the time/intervention (four moments) as the intra-subject factor, and the five covariates. This analysis will test the main and interaction effects between these two factors.

We also aim to carry out the described procedure using only the three moments T1, T2, and T3 and consider T0 an additional covariate. We will proceed with their decomposition if significant time or interaction effects exist.

Finally, a latent growth model will be tested to assess the trajectory (linear and quadratic) of the study participants concerning outcomes and how this trajectory is conditioned by the factors that originate the groups.

Statistical analysis will be performed using IBM SPSS Statistics V28 and IBM SPSS Amos V28, and p values < 0.05 will be considered significant.

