The PR programme’s benefits tend to wane after six months due to patients’ failure to adopt necessary behaviour changes [14–16]. Developing self-efficacy perception and self-management skills of the disease are vital issues to change patients’ health-related behaviours [5, 14, 17]. . However, this strategy alone has proven ineffective for all patients. Incorporating behavioral change techniques, such as physical activity diaries, is paramount to enhance the effectiveness of health interventions. These diaries can provide personalised and daily goals for each patient, ensuring a more effective path to change [18]. Therefore, action is needed to ensure that, after finishing PR programmes, patients will maintain disease control behaviours throughout time, their functionality level, and their health-related quality of life [19].

In response to the challenge of diminishing PR effects over time, the concept of PR maintenance programmes emerged as a promising solution [20–23]. It is also suggested that these programmes should be offered in a home-based setting, particularly to severe patients, for twelve or more months and should be supervised [24].

In the current Portuguese primary health care context, community care units can provide multidisciplinary care to patients with COPD. These units have a multidisciplinary team, including nurses specialists in rehabilitation, whose competencies enable prescribing and delivering PR programmes, as certified by the Portuguese Order of Nurses [25]. These community care units are geographically well-distributed across the country [26].

Therefore, rehabilitation nurses have an essential role in developing structured and multidisciplinary PR programmes that may achieve the needs of patients, even the most severe patients whose functional limitation is more pronounced and those more complex due to multimorbidity [27, 28].

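### The sample size was derived for the group difference at T3; it does not carry over to the group main effect of the four-moment mixed ANCOVA, which averages in two visits taken before the arms diverge

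*Protocol article*

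**What the plan says.** Under Sample size and statistical methods, the required number "was calculated considering the final comparison between the two groups regarding the primary outcome". The inputs are ANCOVA, 5% significance, 80% power, f = 0.25 and "five covariates in the model, the sample size to be collected will be 128 participants". Allowing for 20% loss raises this to 160.

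Under Data analysis, the article opens with "The sample size covers the sample dimension necessary for applying a mixed ANCOVA". Group is the between-subject factor, the four moments T0–T3 are the within-subject factor, and there are five covariates. It continues: "This analysis will test the main and interaction effects between these two factors". A second version of the model uses T1, T2 and T3 only, with T0 as a further covariate. Significant time or interaction effects are to be decomposed.

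Under Assignment of interventions, T0 precedes the initial programme, T1 coincides with randomisation at eight weeks, T2 is at seven months and T3 at 12 months. Under Study setting, everyone receives the same eight-week programme before one group goes on to maintenance.

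**The concern.** The number was calculated for one comparison and is then said to serve a model that tests several effects. One of these, the group main effect, is a different quantity from the T3 difference. In a mixed ANCOVA it is the group difference averaged over all moments in the model. Maintenance cannot influence T0 or T1, so the expected difference is zero at two of the four moments.

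What is at stake is interpretation. A reader who is told that the sample size covers this model could take a non-significant group effect as evidence against maintenance. With a true T3 difference of exactly the planned size, non-significance would be the likelier result. If the averaged difference were also reported as the treatment effect, it would be a quarter to a half of the true T3 difference.

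**Working it through.** **Inputs from the article:** alpha 0.05, f = 0.25 (0.5 residual SD for two equal groups), five covariates, N = 128 (64 per group by arithmetic), four moments, expected difference zero at T0 and T1.

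**Assumptions not in the article:** equal correlation rho between visits of 0.5–0.8, and a T2 difference of 0, 0.25 or 0.5 SD.

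**1. The article's own figure.** Noncentrality lambda = N × f² = 128 × 0.0625 = 8.0, with 1 and 128 − 2 − 5 = 121 df. Power is 80.1%, and 128 is the smallest N that reaches 80%. Then 128 / 0.80 = 160. Both figures reproduce.

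**2. Group main effect, four moments.** This is an ANCOVA on each patient's mean over visits.
- Mean difference = (0 + 0 + T2 + 0.5) / 4, which is 0.125, 0.1875 or 0.25 SD.
- Variance of a four-visit mean = (1 + 3 rho) / 4, which is 0.625 at rho 0.5 and 0.85 at rho 0.8.
- lambda = (N/4) × (mean difference)² / variance, with 1 and 121 df.
- Example, full effect at T2 and rho 0.5: 32 × 0.0625 / 0.625 = 3.2, power 42.7%.
- Example, effect at T3 only and rho 0.8: 32 × 0.015625 / 0.85 = 0.59, power 11.9%.

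| T2 difference | rho 0.5 | rho 0.7 | rho 0.8 |
|---|---|---|---|
| 0 | 14.4% | 12.5% | 11.9% |
| 0.25 SD | 26.5% | 22.3% | 20.7% |
| 0.5 SD | 42.7% | 35.7% | 33.1% |

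Simulation agreed: 41.9% for a T2 difference of 0.5 SD at rho 0.5, and 33.3% at rho 0.7.

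**3. Sensitivity.** At rho 0.3 the range is 17.5–53%, and at rho 0.9 it is 11–31%. A correlation that decays with distance between visits (lag-one 0.5–0.9) gives 12–50%. Power reaches 80% only with uncorrelated visits and the full effect already at T2. Taking the stated 69 per group (N = 138) gives 12–45%. Retaining all 160 gives 14–51%.

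**4. Effect needed for 80%.** For f = 0.25 measured against the SD of the four-visit mean, the average must be 0.5 × √((1 + 3 rho)/4), or 0.40–0.46 SD. With zero at T0 and T1, that means twice as much at both T2 and T3: 0.79 SD at rho 0.5 and 0.92 SD at rho 0.8.

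**5. Three-moment model.** The mean difference is (0 + T2 + 0.5) / 3, from 0.167 to 0.333 SD, so at least one third of the T3 difference is lost. Power depends on how the planned 0.5 SD is scaled:
- SD before T0 adjustment: variance (1 + 2 rho)/3 − rho², power about 30–98%.
- SD after T0 adjustment: variance (1 + 2 rho)/3, power about 17–63%.

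**6. Group-by-time interaction.** lambda = (N/4) × Σ(difference at each visit − mean difference)² / (1 − rho).
- Weakest four-moment case (half the effect at T2, rho 0.5): 32 × 0.1719 / 0.5 = 11.0 on 3 and 363 df, power about 80%.
- Weakest three-moment case (same pattern): 32 × 0.125 / 0.5 = 8.0 on 2 and 240 df, power about 71%.
- At rho 0.8, power is 98% or more in both models.

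**The case against.** The coverage sentence attaches no power to the group main effect under any particular pattern of visits. If 0.5 of a single-visit SD is placed directly on the visit average, 128 patients give 86–94% power at rho 0.5–0.8, and on that conventional reading the sentence is true. The point stands as a matter of wording: the sentence is not flatly false on every reading. It does not rescue the design, though. With zero at T0 and T1, that average needs 4 × 0.5 / 2 = 1.0 SD at both T2 and T3, and even bare 80% power needs 0.79–0.92 SD at both, against a planned 0.5 SD at T3.

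The group main effect is also not the natural test of the hypothesis. The Discussion expects slower fading, which is an interaction, and only time or interaction effects are to be decomposed. This stands, and it limits the finding to one named term of the model. Nor does the article say that the averaged difference will be reported as the treatment effect, so that harm is a risk rather than a stated plan.

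Two stronger readings are tempting. One is that the trial is underpowered. The documents do not support it: the T3 calculation reproduces and the interaction is mostly well powered. The other is that T3 will carry nearly all the difference, because "benefits tend to wane after six months" (Introduction) and T2 comes only about five months after the initial programme ends (7 × 52/12 − 8 = 22.3 weeks). The Abstract places the decline at six to twelve months, and neither statement fixes the size of the T2 difference. It has to remain a range.

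**Conclusion.** The point holds in a limited form. The power statement belongs to the T3 group difference and does not extend to the group main effect of the four-moment mixed ANCOVA. A planned 0.5 SD at T3 becomes 0.125–0.25 SD on the average, with power of about 12–43%. That range rests on the assumed visit correlation of 0.5–0.8 and the assumed T2 difference of 0–0.5 SD. A shortfall at the planned effect size does not depend on the exact correlation, since any positive common correlation leaves power below 80%.

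The three-moment group effect is also diluted, but its power ranges from 17% to 98% across the two scalings and the assumed patterns, so no single figure should be claimed. The interaction (about 71–100%) is mostly adequate.

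**What to change.** Four changes under Sample size and statistical methods and Data analysis:
- Replace the coverage sentence with a statement that the sample size is for the group comparison at T3 only.
- Name the T3 contrast or the group-by-time interaction as the test of maintenance.
- State that a group main effect averaged over visits that include T0 or T1 will not be read as evidence for or against maintenance.
- Where a group effect is reported, use T2 and T3 as outcomes and T0 and T1 as covariates.

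The cost is a narrower power statement and a small change to the fitted contrast, so this is slightly more than rewording. The data are already to be collected, and no further patients or visits are needed. Averaging T2 and T3 corrects what is estimated but does not guarantee 80% power: if the effect appears only at T3, that average is half the T3 difference.

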### Assignment of interventions

After the patient’s informed consent, allocation concealment will be ensured by opening a well-sealed envelope. The trial was registered on March 21st 2022 at ClinicalTrials.gov (NCT05315505), and this protocol is reported according to the SPIRIT guidelines.

Outcomes will be measured at four time points (T0, T1, T2 and T3) with a cardiopulmonary technician, who will not be aware of the group allocation. Every assessment will take place in the regional hospital.

The first assessment (T0) will occur before the initial PR programme. After eight weeks, the subjects will be reassessed at T1 during randomisation. At seven months, corresponding to the intermediate period of the maintenance PR programme, the subjects will be reassessed at T2 and T3 at 12 months, corresponding to the end of the study.

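### The 80% power belongs to a single final ANCOVA, but the planned tests are mixed ANCOVAs that keep visits before the groups diverge as outcomes; name the 12-month difference adjusted for T1 as primary

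*Protocol article*

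**What the plan says.** Under Sample size and statistical methods, the Protocol article states the basis for its numbers: "The minimum sample size required was calculated considering the final comparison between the two groups regarding the primary outcome". The inputs are an ANCOVA with a 5% significance level, 80% power, f = 0.25 and five unnamed covariates. They give 128 participants, or 160 after allowing for 20% losses.

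Under Data analysis, the first model has four outcome occasions: "The group will be considered an inter-subject factor, the time/intervention (four moments) as the intra-subject factor, and the five covariates". Group and time main effects and their interaction are all to be tested. The procedure is then repeated "using only the three moments T1, T2, and T3 and consider T0 an additional covariate". Significant time or interaction effects are to be decomposed, and a latent growth model follows. No test is called primary. The section opens by asserting that the sample size is enough for a mixed ANCOVA.

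Under Assignment of interventions, T0 precedes the initial programme, and for T1: "After eight weeks, the subjects will be reassessed at T1 during randomisation". Under Methods and analysis, the first 8-week phase goes to both groups.

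**The concern.** Maintenance starts after T1, so a treatment effect can appear only at T2 and T3. A group difference at T0 or T1 is chance imbalance, which is a reason to adjust for T1. Both mixed ANCOVAs instead keep T1 as an outcome level. The second adjusts for T0, the value before the shared programme, rather than for the value at which the groups part.

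Two things are at stake. First, the four-moment group main effect mixes two visits without a treatment effect with two that may have one, so its estimate is not the effect at any visit. Read as the test of maintenance, it could miss a real benefit. Second, the stated power belongs to a 1-df comparison at the final visit. The sample size inputs include no between-visit correlation and no effect at T2, so they cannot fix the power of any repeated-measures test.

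**Working it through.** **Inputs from the protocol.** Two equal groups, alpha 0.05, power 0.80, f = 0.25, five covariates, N = 128. For two equal groups, d = 2f = 0.50 SD.

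**Assumptions, not in the protocol.** Between-visit correlation ρ of 0.5–0.9, equal for all pairs unless stated. T3 difference 0.50 SD. T2 difference 0.25 SD (half of T3) or 0.50 SD (sustained). T0 and T1 differences are zero by design. SD is 1 at each visit, and the five covariates cost degrees of freedom only.

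**Step 1: the plan's own figure.** Noncentral F with λ = N·f² = 128 × 0.0625 = 8, df = 1 and 128 − 2 − 5 = 121. Power is 0.801, so N = 128 reproduces, and 128/0.8 = 160. This is the power of one comparison at one visit.

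**Step 2: four-moment group main effect.** The test compares person means over four visits.
- Mean difference: (0 + 0 + 0.25 + 0.50)/4 = 0.1875 SD, or (0 + 0 + 0.50 + 0.50)/4 = 0.25 SD.
- Variance of a person mean: (1 + 3ρ)/4, which is 0.625, 0.775 and 0.925 at ρ = 0.5, 0.7 and 0.9.
- λ = (N/4) × (mean difference)²/variance, with df = 1 and 121.

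| ρ | T2 = 0.25: λ | power | T2 = 0.50: λ | power |
|---|---|---|---|---|
| 0.5 | 1.80 | 0.27 | 3.20 | 0.43 |
| 0.7 | 1.45 | 0.22 | 2.58 | 0.36 |
| 0.9 | 1.22 | 0.19 | 2.16 | 0.31 |

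Even with the effect sustained, 80% power for this test would need about 316 participants at ρ = 0.5 and 468 at ρ = 0.9.

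**Step 3: four-moment group-by-time test (3 df).** λ = (N/4)·δ′W⁻¹δ, where δ holds the group differences in change from T0 and W is the covariance matrix of those changes.
- Equal correlation: power 0.79 (ρ = 0.5, T2 = 0.25) to above 0.99.
- First-order autoregressive correlation: 0.50 (ρ = 0.5, T2 = 0.25) to above 0.99.

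**Step 4: three-moment version with T0 as covariate, equal correlation.** Group main effect 0.58 to above 0.99; interaction 0.71 to above 0.99.

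**Step 5: the T3 contrast itself, N = 128, equal correlation.**
- Change from T1 to T3: variance 2(1 − ρ), λ = 8/[2(1 − ρ)]. At ρ = 0.5, λ = 8.0 and power is 0.80; at 0.7, λ = 13.3 and 0.95; at 0.8, λ = 20 and 0.99.
- T3 adjusted for T1: residual variance 1 − ρ², λ = 8/(1 − ρ²). At ρ = 0.5, λ = 10.7 and power is 0.90; at 0.7, λ = 15.7 and 0.98.

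The Step 5 figures take f = 0.25 as the effect before adjustment for T1. If f already includes that adjustment, the power of the adjusted T3 comparison stays at 0.80.

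**The case against.** The strongest reply is that the four-moment group main effect need not be the effectiveness test. The plan calls no model main or primary. The Discussion expects benefits to fade more slowly with maintenance, which is an interaction hypothesis, and the interaction is planned. Decomposing it can give the group difference in T1-to-T3 change, a valid contrast that takes account of T1 and has power of 0.80 or more in Step 5. The four-moment model also serves a second stated expectation, benefit over the first eight weeks. The sample size section already names a final ANCOVA, and its unnamed covariates might include T1 walk distance.

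Most of this stands, and it rules out several stronger readings. A reader might infer that the main analysis is diluted, that every planned test is underpowered, or that no planned route reaches the T3 contrast. The documents support none of these. Nor do they establish that adjusting for T1 must raise power, since that depends on what f = 0.25 represents.

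The reply leaves three things open. The group main effect is still a planned test. The T3 contrast is reached only through a significant omnibus result. And the final ANCOVA that was sized does not reappear under Data analysis, where T1 is an outcome level in both mixed models. These points concern what the article states, so they do not depend on detail that an unseen analysis plan might add.

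**Conclusion.** The concern holds as a mismatch between the comparison that was sized and the tests that are planned. The 80% is correct for a 1-df final comparison (0.801 at N = 128). It does not carry over to the mixed ANCOVAs, and the assertion that the sample size suffices for them is unsupported.

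The four-moment group main effect should not be read as the test of maintenance. It turns 0.50 SD at T3 into about 0.19–0.25 SD, with power of about 0.2–0.4. Those figures rest on the assumed equal correlation of 0.5–0.9 and T2 effect of 0.25–0.5 SD. The direction of the dilution does not, because T0 and T1 precede the divergence of the groups.

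The group-by-time test is usually adequately powered under equal correlation, though less surely if correlation decays over time. Its weakness is that it is an omnibus gate and does not itself estimate the 12-month difference.

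**What to change.** - Name as the single primary analysis the group difference in 6-minute walk distance at T3, with T1 (and T0) walk distance as covariates. It can come, for example, from a model in which only T2 and T3 are outcome occasions.
- Attach the 80% power statement to that contrast, and say whether f = 0.25 is the effect before or after adjustment for T1. Power is at least 80%, and about 90–98% at a T1–T3 correlation of 0.5–0.7 if it is the effect before adjustment.
- Delete the assertion that the sample size suffices for the mixed ANCOVA, or support it with a stated correlation and T2 effect.
- Keep both mixed ANCOVAs and the latent growth model as supportive, including for the T0-to-T1 change, and state that the four-moment group main effect is not interpreted as the maintenance effect.

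The cost is a change of wording. All four measurements are already planned, and no participants or visits are added.

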### Methods and analysis

Our study is a randomised controlled trial with two parallel groups. The Rehab2Life programme includes two distinct phases. The first is an 8-week PR programme delivered to both groups, and the second is an additional PR maintenance programme given to the intervention group.

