### Study setting

The study will occur in four community care units in a Portuguese urban area. All participants will undergo an 8-week home-based PR programme, after which one group will remain in a maintenance programme (intervention group). The other will have access to usual care (control group). Figure 1 – Flow diagram.

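### Both mixed ANCOVAs treat T1, the value at randomisation, as an outcome moment, so the group main effect is diluted and the valid interaction test gives up precision that adjusting for T1 would recover

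*Protocol article*

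**What the plan says.** The protocol article sets the timing out clearly. Under Methods and analysis: "The first is an 8-week PR programme delivered to both groups, and the second is an additional PR maintenance programme given to the intervention group". Under Assignment of interventions, "The first assessment (T0) will occur before the initial PR programme", then "After eight weeks, the subjects will be reassessed at T1 during randomisation"; T2 comes at seven months and T3 at 12 months. The arms are therefore treated alike up to T1, and only T2 and T3 follow the point where they diverge.

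The Data analysis section lists two mixed ANCOVAs. The first has group as the between-subject factor, all four moments as the within-subject factor, and five covariates that the article does not name. Of this model it says: "This analysis will test the main and interaction effects between these two factors". The second repeats the procedure "using only the three moments T1, T2, and T3 and consider T0 an additional covariate". Significant time or interaction effects are then to be decomposed, and a latent growth model follows. Neither mixed model has T1 as a covariate.

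The sample size section rests on something simpler, an ANCOVA "calculated considering the final comparison between the two groups regarding the primary outcome".

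**The concern.** At T1 the true difference between the arms is zero by design, because patients are randomised then and have had the same treatment until then. Counting T1 as an outcome moment has three consequences.

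- **Dilution.** The group main effect averages a known zero with the moments at which an effect can exist.
- **Carry-over.** T0 precedes the 8-week response. Adjusting for it removes only the part of a chance T1 difference that T0 predicts, and the rest enters the main effect.
- **Precision.** The group-by-time interaction uses T1 as the point from which change is measured. Change from baseline is usually less precise than adjustment for baseline, and it over-corrects a baseline imbalance.

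At stake is how well the 6-minute walk comparison uses data that will be collected anyway, and whether a reader who takes the group main effect as the maintenance effect is misled about its size.

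**Working it through.** **1. The plan's own figure.** Inputs from the sample size section: f = 0.25, alpha 5%, power 80%, five covariates. Noncentral F with 1 and 128 - 2 - 5 = 121 df and noncentrality f²N = 0.0625 × 128 = 8 gives power 0.801, so 128 reproduces. With 0 or 6 covariates power is still 0.801. For two equal groups f = 0.25 is a standardised difference of 0.5. I use 128/2 = 64 per arm. (The article's 69 per group does not match 128; that is a separate point.)

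**2. Dilution.** This needs no correlation assumption. Let d be the effect at T3. T1 falls at about 2 months, so T2 at 7 months is (7 - 2)/(12 - 2) = 1/2 of the way to T3.

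| Model | Steady effect (d at T2 and T3) | Linear growth (d/2 at T2, d at T3) |
|---|---|---|
| Three moments | (0 + d + d)/3 = 2d/3 | (0 + d/2 + d)/3 = d/2 |
| Four moments | (0 + 0 + d + d)/4 = d/2 | (0 + 0 + d/2 + d)/4 = 3d/8 |

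**3. Assumptions for power.** Multivariate normal, SD 1 at each moment. Correlations are either equal (0.6, 0.7, 0.8) or decaying: T0-T1 0.75, T0-T2 0.65, T0-T3 0.60, T1-T2 0.80, T1-T3 0.75, T2-T3 0.85. None of these is in the document. I set d = 0.5 × √(1 - r²), with r the T0-T3 correlation, so that T3 adjusted for T0 alone has the planned 0.801. This gives d = 0.400, 0.357, 0.300 and, for the decaying pattern, 0.400.

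Noncentrality is (64/2) × δ'V⁻¹δ, where δ is the effect on the tested contrasts and V their residual covariance given the covariates.

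**4. One case in full** (equal correlation 0.6, steady effect, d = 0.4). Given T0, each variance is 1 - 0.36 = 0.64 and each covariance 0.6 - 0.36 = 0.24.

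- T3 given T0: 32 × 0.16/0.64 = 8.0, the planned value; power 0.801.
- Three-moment main effect: target 0.267, variance (3 × 0.64 + 6 × 0.24)/9 = 0.373; 32 × 0.0711/0.373 = 6.1; power 0.688.
- Interaction, 2 df: T2 - T1 and T3 - T1 each have variance 0.80 and covariance 0.40; 32 × 2 × 0.16/1.20 = 8.5; power 0.736.
- Adding T1 as covariate: variance 0.64 - 0.24²/0.64 = 0.55, covariance 0.24 - 0.09 = 0.15. T3 alone: 32 × 0.16/0.55 = 9.3; power 0.857. T2 and T3 jointly, 2 df: 32 × 2 × 0.16/0.70 = 14.6; power 0.933.

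**5. All eight scenarios** (power; the third decimal depends on how residual df are counted):

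| Correlation | Effect | Main effect, T1-T3 | Interaction, T1-T3 | T3 given T0, T1 | T2 and T3 jointly given T0, T1 |
|---|---|---|---|---|---|
| 0.6 | steady | 0.688 | 0.736 | 0.857 | 0.933 |
| 0.6 | growing | 0.451 | 0.603 | 0.857 | 0.798 |
| 0.7 | steady | 0.670 | 0.763 | 0.869 | 0.937 |
| 0.7 | growing | 0.437 | 0.631 | 0.869 | 0.809 |
| 0.8 | steady | 0.655 | 0.788 | 0.880 | 0.942 |
| 0.8 | growing | 0.424 | 0.657 | 0.880 | 0.820 |
| decaying | steady | 0.634 | 0.931 | 0.926 | 0.955 |
| decaying | growing | 0.408 | 0.841 | 0.926 | 0.872 |

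The like-for-like comparison is between the two 2-df tests. There the T1-adjusted test is ahead in every row, by as little as 0.024 and as much as 0.197.

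**6. Carry-over.** Let b be the regression of a later moment on T1 given T0. With equal correlation r, b = r/(1 + r); at 0.6, b = 0.375. One unit of T1 imbalance not explained by T0 shifts the three-moment main effect by (1 + 0.375 + 0.375)/3 = 0.583 and the T3 - T1 contrast by 0.375 - 1 = -0.625. In the decaying pattern b is (0.80 - 0.75 × 0.65)/0.4375 = 0.714 at T2 and (0.75 - 0.75 × 0.60)/0.4375 = 0.686 at T3. The shifts are then 0.800 and -0.314. With T1 as a covariate both are zero.

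**The case against.** The strongest reply is that the main effect is not the test of maintenance. The Discussion expects benefits gained in the first eight weeks to fade more slowly with the maintenance phase. That is a difference in change from T1, and the interaction over T1, T2 and T3 tests it directly and without dilution. The decomposition can yield a T3 comparison adjusted for T0, which under the working assumptions has the planned 80% power. The growth model also addresses trajectory. With decaying correlations and a steady effect the interaction (0.931) even slightly exceeds T3 adjusted for T0 and T1 (0.926). Which contrast is primary may be settled in an analysis plan that is not shown.

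Most of this stands, and it rules out several stronger readings that a reader might infer:

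- *That the trial's primary effect will be understated whichever test is used.* Dilution and direct carry-over affect only the group main effect, and the article does not name that as the primary contrast.
- *That adjusting for T0 does nothing about a T1 imbalance.* It removes the part that T0 predicts.
- *That chance imbalance at T1 produces extra false positives.* Under randomisation the type I error is not inflated. The issue is imbalance conditional on the T1 values observed.

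What remains is that the article commits to testing the main effect in models where it is diluted. Its undiluted test is less precise than the like-for-like T1-adjusted test in all eight scenarios. Decomposition also depends on a significant time or interaction effect. Calling the three-moment model secondary does not help, because the four-moment model dilutes the main effect more.

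**Conclusion.** The point holds as a should-fix. The dilution fractions (2/3 or 1/2 with three moments, 1/2 or 3/8 with four) follow from the design and the two effect shapes alone. The precision loss rests on assumed correlations and 64 evaluable patients per arm: 60-93% power for the interaction against 80-96% for the joint T2-T3 test given T0 and T1. The gap could be small if correlation decays with time. The plan does contain a valid test of its hypothesis. The harm is a diluted main effect, lost precision and sensitivity to chance imbalance at T1, not an invalid trial.

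**What to change.** For the randomised comparison, replace both mixed models with one that has only T2 and T3 as outcome moments and takes T1 and T0 6-minute walk distance as covariates. Report the adjusted group difference at T3 with its 95% CI, which matches the final between-group comparison by ANCOVA that sized the trial. State whether T1 takes one of the five covariate places or is added to them; step 1 shows that one covariate more leaves the 128 unchanged. Describe the T0-T1 gain separately, as a within-patient change during a programme given to everyone. Treat each secondary outcome measured at T1 in the same way.

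The cost is wording only. T1 is already scheduled at randomisation, and neither visits nor sample size change.
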